##### Sample size {14}

Previous studies have shown a resolution of NASH in the 85% of patients undergoing a bariatric surgery (69.6% in gastric tubing surgery) and a resolution of 25% in patients with a lifestyle intervention. A bilateral ratio comparison test was used for sample size calculation with a confidence level of 99%, a statistical power of 90%, and an assumption of 7% loss. Obtained sample to observe differences is *n*=30 (15 per treatment arm).

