### Statistical methods

#### Statistical methods for primary and secondary outcomes {20a}

Data will be analyzed using SPSS version 19. A descriptive baseline and end-of-follow-up analysis (week 96) of the data will be performed using the mean and standard deviation or the median and range where appropriate for quantitative data and percentage for qualitative data. Quantitative variables will be compared with Student’s *t* test and qualitative variables will be compared with *X*^2^. When variables do not follow a normal distribution, non-parametric tests should be used. Paired data tests will be used to analyze baseline and 96-week results.

All changes in efficacy parameters endpoints will be analyzed in an intention-to-treat and per-protocol analysis and grouped by randomized treatment.

The Intent-to-Treat (ITT) population will include all subjects randomized to treatment. The per-protocol (PP) population will be a subset of the ITT population, excluding subjects that violate key protocol criteria, with the exact list of exclusion reasons to be included in the statistical analysis plan (SAP).

The primary efficacy endpoint, by histopathological improvement of fibrosis by at least 1 stage without any worsening of NASH, and histopathological resolution of NASH without any worsening of the stage of fibrosis will be conducted on the intention-to-treat (ITT) population; so all randomized subjects will be included in the primary analysis.

Secondary endpoints analyzed by descriptive statistics and inferential statistics will include ANOVA. Non-parametric tests may be utilized such as Wilcoxon rank-sum.

For all tests, we will use 2-sided *p* values with alpha < 0.05 level of significance.

All safety variables (i.e., adverse events, laboratory data, vital signs, and ECG) will be summarized by treatment for all patients of the safety set. Descriptive statistics using appropriate summary statistics will be calculated for quantitative safety data as well as for the difference to baseline, when appropriate. In addition, a shift table describing out-of-normal range shifts will be provided for clinical laboratory results.

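### The sample size is planned at two-sided alpha 0.01 but every test is run at 0.05; at 0.01 the planned chi-square test has about 82–85% power for 85% versus 25%, not the stated 90%

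*Protocol article*

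**What the plan says.** Protocol article, Sample size {14}: the calculation is a two-sided comparison of two proportions, made "with a confidence level of 99%, a statistical power of 90%, and an assumption of 7% loss". The result is 30 patients, 15 per arm. Two sources of rates are cited just before. For surgery the text reports "resolution of NASH in the 85% of patients undergoing a bariatric surgery (69.6% in gastric tubing surgery". For lifestyle intervention the rate given is 25%. The paragraph does not say which pair of rates was entered or which form of the two-proportion formula was used.

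Protocol article, Statistical methods for primary and secondary outcomes {20a}: categorical variables are compared by chi-square, the primary analysis includes all randomized subjects, and "For all tests, we will use 2-sided *p* values with alpha < 0.05 level of significance".

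No sentence explains why the planning level and the testing level differ.

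**The concern.** A two-sided test at 99% confidence has alpha 0.01. The analysis section sets 0.05 for all tests, which includes the primary one. Two significance levels are therefore attached to the same comparison, and the 90% power is tied to the one that the analysis does not use.

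Two things follow. First, a reader cannot tell what type I error the primary comparison was meant to have. In a trial of this size the gap between the levels covers ordinary results: with 15 per arm, 13 versus 7 resolutions gives an uncorrected chi-square of 5.40 (p = 0.020), and 12 versus 6 gives 5.00 (p = 0.025). Both lie between 0.01 and 0.05. Second, the stated power should describe the test that will be run. If it does not hold for that test at the stated level, the figure needs correcting.

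**Working it through.** **Inputs** (Sample size {14} unless noted)
- Rates: p1 = 0.85, p2 = 0.25. This pair is inferred; it is the one that reproduces 30.
- Two-sided alpha 0.01, so z = 2.576; power 90%, so z = 1.282.
- Loss 7%; allocation 1:1 (Trial design {8}).
- Planned test: chi-square (Statistical methods {20a}).

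**Step 1. Reproduce the plan's figure.** Unpooled normal approximation:

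n = (z_α + z_β)² × [p1(1−p1) + p2(1−p2)] / (p1−p2)²

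= (2.576 + 1.282)² × (0.1275 + 0.1875) / 0.36 = 13.02, so 14 per arm.

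Loss: 14 × 1.07 = 14.98, so 15 per arm and 30 in total. The plan's figure is reproduced. (Dividing instead, 14 / 0.93 = 15.05, which rounds up to 16 per arm, 32 in total.)

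**Step 2. The formula that matches a chi-square test.** Pooled variance under the null, with mean rate 0.55:

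n = [2.576 × √(2 × 0.55 × 0.45) + 1.282 × √0.315]² / 0.36 = 17.80, so 18 per arm, or 20 with loss (40 in total).

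At the same alpha and power, the arcsine formula also gives 18 per arm, and the continuity-corrected formula gives 22. With 69.6% in place of 85%, even the unpooled formula needs 30 per arm before loss. So at 0.01 the figure of 30 rests on the unpooled form and on the 85% rate.

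**Step 3. Power by formula at alpha 0.01.** With 14 per arm the unpooled standard error is √(0.315/14) = 0.150. Then 0.60/0.150 − 2.576 = 1.424, which is 92.3% power. The pooled form gives 78.0%. With 15 per arm the two are 94.1% and 81.9%.

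**Step 4. Exact power.** Every pair of binomial outcomes was enumerated for 85% versus 25%, and the probabilities of those rejected by the uncorrected Pearson chi-square test were summed.

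| Per arm | alpha 0.01 | alpha 0.05 |
|---|---|---|
| 14 | 82.1% | 92.2% |
| 15 | 84.7% | 94.5% |
| 17 | 87.8% | 97.4% |
| 18 | 91.4% | 98.3% |

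Fourteen per arm is the count after the assumed loss; 15 is the number randomized.

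**Step 5. Is the shortfall only a matter of the pooled form?** No. An unpooled Wald test, which is the test the unpooled formula describes, has exact power at 0.01 of 85.1% with 14 per arm and 87.7% with 15. The approximation promised 92.3% and 94.1%. It is optimistic at this size even on its own terms.

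**The case against.** The strongest reply is that nothing has been miscalculated. A standard formula with the plan's own inputs returns exactly 30, and the article names no variance form that would make this wrong. That stands. A reader might infer an arithmetic slip, and Step 1 shows there is none. What remains is that the formula's answer does not carry 90% power for the planned test at 0.01.

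A second reply is that the sample size paragraph gives a planning input and not a rule for declaring success. The only written decision rule is 0.05, and it covers all tests. That also stands. A reader might infer that the success threshold is open by a factor of five and could be picked after the data are seen. The article does not support this, because it contains no second decision rule. A p-value of 0.02 is significant under the rule as written.

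A third reply is that planning at a stricter level than the one tested can only help power for a given n. This is correct, and the right-hand column of the table shows it: for these rates the 90% is exceeded at 0.05. The reply does not remove the inconsistency, because a reader of the sample size section is told of 99% confidence and the analysis does not apply it.

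Lower figures are available from Fisher's exact test (68% and 76% at 0.01 with 14 and 15 per arm). The article names chi-square, so they are not the measure of this point.

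Last, it can be objected that restating power at 0.05 as 92–95% would give false comfort, since 85% and 25% come from surgery and lifestyle intervention while the randomized arms are ESG and LSG, both with lifestyle modification. This is a fair warning, and the fix takes it up.

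**Conclusion.** The point holds as an unreconciled significance level with a power figure that does not fit the level attached to it. At 0.01 the planned chi-square test has about 82% power (14 per arm) to 85% (15 per arm), a shortfall of roughly 5 to 8 percentage points. At 0.05, the rule actually written, power is about 92% to 95% and the stated 90% is met.

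These figures assume that 85% and 25% were the rates entered, that the test is the uncorrected Pearson chi-square, and that 14 or 15 per arm are evaluable. They say nothing about the power to detect a difference between ESG and LSG. The correction is worth making because the sample size justification rests on this figure. It does not undermine the design and does not call for more patients.

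**What to change.** State one two-sided alpha for the primary test in both sections.

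- Simplest: rewrite Sample size {14} at alpha 0.05, the level the analysis already uses, and report exact chi-square power of about 92% with 14 evaluable per arm and 95% with 15.
- If 0.01 is intended: set 0.01 for the primary test in Statistical methods {20a}, and restate power in Sample size {14} as about 82% to 85%.

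In either case, name the two rates and the formula or method used. Add one sentence saying that the power refers to a difference of 85% versus 25% taken from surgery and lifestyle data, and is not the power for an expected ESG versus LSG difference.

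Cost: a sentence or two in each section. There is no change to the number of patients, and no change to the analysis unless 0.01 is chosen. The choice should be recorded before outcome data are examined.

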##### Recruitment {15}

Potential candidates will be reviewed in daily consultation by the gastroenterologist and endocrinologist. Patients with obesity, with or without metabolic syndrome and a NASH diagnosed by liver biopsy, will be evaluated.

### Assignment of interventions: allocation

#### Sequence generation {16a}

Randomization will be carried out on all eligible subjects using a computer system. At the randomization visit, eligible subjects will be randomized 1:1 for the following groups:
Experimental group: ESG + lifestyle modificationsControl group: LSG + lifestyle modifications

Randomization will be stratified into 2 strata defined by diabetes status

#### Concealment mechanism {16b}

Once the patient is selected for inclusion in the study by the site’s investigator and eligibility has been evidenced, the study coordinator will proceed with the randomization of the patient by writing an email to the following email address: [contact]. The person in charge of the list will reveal the patient’s assigned code, taking into account the stratification in terms of the presence or absence of diabetes type 2, along with the assignment to the experimental or control intervention. The person in charge of this list is an employee of the same institution but not involved in the selection of patients.

#### Implementation {16c}

Non-recruitment involved staff will inform the study coordinator of the randomization number and treatment group assigned. Then, the patient is notified of the date of the intervention.

#### Assignment of interventions: blinding

Given the nature of this study where surgical procedures are performed versus an endoscopic procedure, the study staff cannot be blinded.

#### Who will be blinded {17a}

Not applicable

#### Procedure for unblinding if needed {17b}

Not applicable

#### Data collection and management

##### Plans for assessment and collection of outcomes {18a}

The coordination of the study is carried out by the Clinical Trials agency, on behalf of the study sponsor (IDIVAL). The review of the data is carried out by the Clinical Research Associate (CRA) from SCReN (Spanish Clinical Research Network) according to the monitoring plan to ensure the validity of the results obtained.

Deviations detected during study monitoring will be reported to the regulatory authorities according to their severity, classified as mild or serious.

Serious deviations are defined as procedures that affect the safety, rights, and welfare of the patients included in the study as well as the quality and integrity of the data obtained, while minor deviations are defined as procedures that do not affect the safety, rights, and welfare of the patients or the quality of the data obtained.

##### Plans to promote participant retention and complete follow-up {18b}

All patients included in the study will be followed for 96 weeks after the intervention (control vs. experimental) to guarantee the patient’s safety, and all the obtained data will be recorded.

Patients who withdrawn from the study because of the criteria mentioned in section 11b will be followed according to the daily clinical practice of the site.

##### Data management {19}

Data collection will be carried out by the study coordinator and the data obtained will be monitored by the CRA. Study-generated data will be collected in a paper case report form (CRF) ad hoc.

##### Confidentiality {27}

In order to avoid any association of personal data with the data obtained, patients will be anonymized by alphanumeric code (Site (01)-01). The research team will have access to the data of patients included in the study, and a list with patients’ identification will be done and keep on the investigator’s file. All the generated data will be recorded in the CRF in an anonymized form.

Personal data will be processed in accordance with Regulation (EU) 2016/679 of the European Parliament and of the Council of 27 April 2016 on the protection of individuals with regard to the processing of personal data and on the free movement of such data, and the relevant local laws.

The data collected for the study shall be identified by an alphanumeric code (Site (01)-01) in such a way that it is not possible to identify the patient. Only the investigator and authorized persons involved in the study will have access to this code and undertake to use this information exclusively for the purposes of the study. All the generated data will be recorded in the CRF in an anonymized form.

Members of the Clinical Research Ethics Committee or Health Authorities may have access to this information in compliance with legal requirements. The confidentiality of this data will be preserved, and it cannot be linked to personal data, even if the results of the study are published.

##### Plans for collection, laboratory evaluation, and storage of biological specimens for genetic or molecular analysis in this trial/future use {33}

Not applicable

### Statistical methods

#### Statistical methods for primary and secondary outcomes {20a}

Data will be analyzed using SPSS version 19. A descriptive baseline and end-of-follow-up analysis (week 96) of the data will be performed using the mean and standard deviation or the median and range where appropriate for quantitative data and percentage for qualitative data. Quantitative variables will be compared with Student’s *t* test and qualitative variables will be compared with *X*^2^. When variables do not follow a normal distribution, non-parametric tests should be used. Paired data tests will be used to analyze baseline and 96-week results.

All changes in efficacy parameters endpoints will be analyzed in an intention-to-treat and per-protocol analysis and grouped by randomized treatment.

The Intent-to-Treat (ITT) population will include all subjects randomized to treatment. The per-protocol (PP) population will be a subset of the ITT population, excluding subjects that violate key protocol criteria, with the exact list of exclusion reasons to be included in the statistical analysis plan (SAP).

The primary efficacy endpoint, by histopathological improvement of fibrosis by at least 1 stage without any worsening of NASH, and histopathological resolution of NASH without any worsening of the stage of fibrosis will be conducted on the intention-to-treat (ITT) population; so all randomized subjects will be included in the primary analysis.

Secondary endpoints analyzed by descriptive statistics and inferential statistics will include ANOVA. Non-parametric tests may be utilized such as Wilcoxon rank-sum.

For all tests, we will use 2-sided *p* values with alpha < 0.05 level of significance.

All safety variables (i.e., adverse events, laboratory data, vital signs, and ECG) will be summarized by treatment for all patients of the safety set. Descriptive statistics using appropriate summary statistics will be calculated for quantitative safety data as well as for the difference to baseline, when appropriate. In addition, a shift table describing out-of-normal range shifts will be provided for clinical laboratory results.

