Regarding the safety of BS in patients with NASH, a wide study carried out on the American Nationwide Inpatient Sample demonstrated that the BS collaborates to a global decrease in the mortality of the patients with NASH [35, 36]. But, despite its beneficial effects, complications can arise. Cholelithiasis represents the most common post-surgical complication, which happens in almost one of every three patients bearing cholecystectomies in a higher proportion than the general population which is associated with higher complications after surgeries, prolongation of hospitalizations, and higher mortality rate.

Therefore, although the facts suggest that the bariatric surgery is useful in patients with NASH, this pathology does not constitute at this moment an established indication for the surgery taking into account that there do not exist randomized clinical trials to evaluate the resolution of NASH as a primary objective with this procedure.

At present, the bariatric endoscopy (BE) has emerged as a new therapeutic option for the treatment of obesity in patients who do not have a surgical indication, refuse it or do not comply with conventional treatments. The OverStitch system (Apollo method) demonstrated in 2013 that the use of this technique was sure and feasible in a pilot study with four patients [37]. Later, a study with 20 patients demonstrated a weight loss in 30% of the patients after 6 months [38].

Experience with the BE is, at the moment, scarce. However, the preliminary results are very good [39]. The development of the Apollo method is new, but it has showed adequate without significant adverse events, discharging the first day after the procedure, with good results in multicenter studies and showing significant weight loss during the first 2 years. Most of the weight loss takes place during the first 6 months after the procedure, and the weight loss is maintained or increased at months 12 and 24 [40]. Even though BE works well across the spectrum of obesity, including subjects with BMI over 40, the duration of the long-term effect is still unknown. Patients who undergo this procedure achieve significant improvement in the high blood pressure (HBP), cholesterol, and HbA1C levels control as well as improved liver function tests and an improvement in their obstructive sleep apnea disorder [40]

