#### Trial design {8}

The TESLA-NASH study is a randomized, controlled, open-label, unicentric clinical trial with a sanitary product, designed to evaluate the efficacy of two gastric techniques (endoscopic versus laparoscopic) in the resolution of NASH without worsening liver fibrosis.
Experimental group: ESG + lifestyle modificationsControl group: LSG + lifestyle modifications

A total of 30 eligible participants will be randomly assigned (stratified by the presence or absence of type II diabetes mellitus) to the experimental group or the control group with a 1:1 ratio. The participants will be recruited at the Hospital Marqués de Valdecilla from June 2020 to June 2021.

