#### Strategies to improve adherence to interventions {11c}

To verify the effectiveness of each technique and ensure patient’s safety, follow-up visits will occur after the interventions. Seven follow-up visits will be carried out over 24 months where the variables described in the protocol will be assessed by means of biochemical cholesterol, biomarkers of inflammation and lipid tests changes, cardiovascular events, quality of life and physical activity questionnaires progress, liver biopsy, abdominal ultrasound and non-invasive assessments of fibrosis, post-intervention dietary and lifestyle recommendations and revisions, records of the concomitant medication during the follow-up, and an evaluation of the safety by controlling adverse events and adverse reactions.

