#### Participant timeline {13}

##### Participant timeline

**Table Tabb:** 

PROCEDURES	WEEK 2	WEEK 8	WEEK 12	WEEK 24	WEEK 48	WEEK 72	WEEK 96
**Liver biopsy**							**X**
**QL questionnaires**					**X**		**X**
**Cardiovascular events**							**X**
**Fecal samples**							**X**
**Blood analysis**		**X**	**X**	**X**	**X**	**X**	**X**
**Safety: SAE and RAE**	**X**	**X**	**X**	**X**	**X**	**X**	**X**
**Dietary recommendations**	**X**	**X**	**X**	**X**	**X**	**X**	**X**
**Fibrosis evaluation**							**X**
**Ultrasound proof**					**X**		**X**

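### Blood is drawn at six visits after the procedure, but the stated efficacy analysis uses only baseline and week 96, so a patient without a week-96 sample cannot enter the promised ITT comparison of the secondary blood endpoints

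*Protocol article*

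**What the plan says.** All references are to the Protocol article.

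- **Participant timeline {13}.** The row "Blood analysis" is marked at six of the seven post-procedure visits: weeks 8, 12, 24, 48, 72 and 96.
- **Strategies to improve adherence {11c}.** "Seven follow-up visits will be carried out over 24 months where the variables described in the protocol will be assessed". The stated purpose covers both effectiveness and safety.
- **Secondary outcomes.** The liver, lipid, glucose, inflammation and other blood markers are defined as evaluations after 96 weeks.
- **Statistical methods {20a}.** "A descriptive baseline and end-of-follow-up analysis (week 96) of the data will be performed", and "Paired data tests will be used to analyze baseline and 96-week results". The tests named are Student's t, ANOVA, rank-sum and paired tests. On analysis sets: "All changes in efficacy parameters endpoints will be analyzed in an intention-to-treat and per-protocol analysis", with ITT meaning everyone randomised. The same section summarises laboratory data by treatment for the safety set, with differences to baseline where appropriate and a shift table.
- **Sample size {14}.** 30 patients, 15 per arm, with 7% loss assumed.
- **Item {20c}.** The question on non-adherence and missing-data methods is answered as not applicable.

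**The concern.** The schedule yields a repeated-measures data set, while the analysis described treats it as two time points. Each named test needs a week-96 value. A patient who leaves after week 72 would have five post-procedure samples on file and still contribute nothing to the between-arm comparison of liver, lipid or glucose markers.

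The plan expects some such patients, offers no method for them, and still promises an analysis of all randomised patients. These statements cannot all hold for the blood endpoints. With 15 patients per arm, each patient who falls out of a comparison counts, and the data that would keep that patient in are being collected anyway.

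**Working it through.** **Sample size and expected loss.** The plan's 30 can be reproduced from its own inputs (85% versus 25%, two-sided 1%, power 90%) with the unpooled normal formula:

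(2.576 + 1.282)² × (0.85×0.15 + 0.25×0.75) / 0.60² = 13.02, rounded up to 14 per arm; 14 × 1.07 = 14.98, so 15 per arm and 30 in total.

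Expected loss: 30 × 0.07 = 2.1 patients, leaving 15 × 0.93 = 13.95 per arm.

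**Draws.** 30 × 6 = 180 after the procedure. Before week 96: 30 × 5 = 150, or 83%.

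**Consistency.** Four statements, side by side:

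1. Secondary endpoints are defined at week 96, and the time points named for their analysis are baseline and week 96 (Secondary outcomes; {20a}).
2. Efficacy changes are analysed by ITT, meaning all randomised ({20a}).
3. 7% loss is expected ({14}).
4. Missing-data methods do not apply ({20c}).

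Given 1, 3 and 4, about two patients have no value to enter, so 2 cannot be met as written.

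**What the interim visits add to the week-96 contrast.** The protocol gives no correlations, so these are assumptions: loss in sequence over time and one common within-patient correlation r from 0.3 to 0.9. With baseline and five interim visits observed (k = 6):

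R² = k r² / (1 + (k−1) r); effective n per arm = 1 / [(1−R²)/m + R²/n], with n = 15 and m the number with a week-96 value.

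| Loss | m | r = 0.3 (R² = 0.216) | r = 0.9 (R² = 0.884) |
|---|---|---|---|
| 7% (plan) | 13.95 | 14.16 | 14.87 |
| 20% (assumed) | 12.0 | 12.54 | 14.58 |

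At 7% loss the gain is 0.21 to 0.92 patients per arm. R² here includes baseline, so the interim visits alone add no more than this. With no loss, m = n and the gain is zero.

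**What is recovered for a lost patient.** Assume correlation rb = 0.4 to 0.6 between baseline and later visits, and rp = 0.6 to 0.9 between any two later visits. After allowing for baseline, later visits correlate at q = (rp − rb²)/(1 − rb²), and five of them explain 5q²/(1 + 4q) of what remains at week 96.

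- rb 0.6, rp 0.6: q = 0.24/0.64 = 0.375; 0.703/2.5 = 28%.
- rb 0.4, rp 0.9: q = 0.74/0.84 = 0.881; 3.880/4.524 = 86%.

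**Average of weeks 48, 72 and 96 against week 96 alone**, both baseline-adjusted. Variance ratio = [(1 + 2rp)/3 − rb²] / (1 − rb²).

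- rb 0.4, rp 0.9: 0.773/0.84 = 0.92, an 8% reduction; 15/0.92 ≈ 16 per arm.
- rb 0.6, rp 0.6: 0.373/0.64 = 0.58, a 42% reduction; 15/0.583 ≈ 26 per arm.

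These two corners are the extremes of the assumed ranges.

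**The case against.** **A fixed week-96 endpoint is a legitimate choice.** It agrees with the way the secondary outcomes are defined, and drawing blood at visits that are not the endpoint is ordinary practice. This stands, and the fix keeps week 96 as the reported result.

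**A reader might infer that the interim samples are not used at all.** The protocol does not support that. Section {20a} summarises laboratory data by treatment, with differences to baseline and a shift table, and does not limit this to week 96. What is missing is a stated efficacy use.

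**A reader might infer that the plan prescribes a complete-case analysis.** It never says so. The t-test, ANOVA and rank-sum sentences name no visit, and an SAP that is not shown may specify a model. However, {20a} defers only the list of per-protocol exclusions to the SAP, and {20c} calls missing-data methods not applicable instead of deferring them. An SAP that added such a method would depart from {20c}.

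**A reader might infer that the plan expects a stable effect from month 12, so that weeks 48 and 72 nearly replace week 96.** The Introduction does say "the weight loss is maintained or increased at months 12 and 24", but that is background on body weight after the endoscopic method. It says nothing about blood markers or the surgical arm.

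**The larger precision figures belong to another quantity.** The 8% to 42% applies to a three-visit average, not to the week-96 contrast, and every correlation is assumed. This also stands.

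**Conclusion.** The point holds as a modest, inexpensive improvement. The stated efficacy tests leave 150 of 180 post-procedure draws without a role in any efficacy comparison. They also cannot include a patient who has no week-96 sample, so the ITT promise, the assumed 7% loss and the answer to {20c} do not fit together for the blood endpoints.

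The practical size is small at the planned loss: about two patients, and less than one effective patient per arm gained at week 96 for within-patient correlations of 0.3 to 0.9. The benefit grows if loss exceeds the plan. For a patient who is lost, the earlier visits recover roughly 28% to 86% of the week-96 information left after baseline, under the assumed correlations.

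The biopsy-based primary outcome is outside this point, because the timeline has no biopsy between baseline and week 96 from which to borrow. The timeline does not say which markers are measured at each draw, so the point covers only those measured repeatedly.

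**What to change.** For blood endpoints measured at several visits, replace the baseline/week-96 tests with one mixed model for repeated measures in all randomised patients who have post-procedure data. Include arm by visit, the baseline value and the diabetes stratum used in randomisation. Choose a covariance structure simple enough for 30 patients and name it in advance. Report the week-96 contrast as the result. An average over weeks 48, 72 and 96 may be pre-specified as a supporting contrast.

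Replace the answer to {20c} with a statement that these endpoints are analysed by this model, and say how patients with no post-procedure value are reported, so that the ITT wording in {20a} matches what is done.

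The cost is protocol or SAP wording and slightly more analysis work; SPSS, the package already named, has a mixed-model procedure. No extra samples, visits or patients are needed. The downside is a covariance assumption between visits, together with the assumption that loss can be explained by the values already observed.
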